### Sample size calculation

In order to investigate the prevalence of MCI or dementia, all individuals currently registered on the local transplant list, who are able to consent and agree to participate in the study, will be included. Currently, this list includes 142 individuals (75 individuals are in status T (transplantable), 67 individuals are in status NT (non-transplantable).

With regard to outcome measures, previous studies have shown highly significant improvements in some domains after transplantation [36], but have not reported effect sizes or statistical parameters that could be used to calculate effect sizes. Harciarek and colleagues [37, 38] report moderate to strong “time × comparison with healthy controls” interaction effects. We therefore conservatively expect to find low to medium effect sizes. For the detection of low to medium (*f* = 0.20) within-person effects with 3 measurement time points and 2 groups using a repeated-measures ANOVA as explained above, a power (1 – *β* (type II error probability) of 0.80 and a type-I error probability (*α*) of 0.05, a sample size of 42 is necessary [39, 40]. We therefore aim for a sample size of 50 persons for the follow-up measurements.

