**Methods:**

We are conducting a prospective single-center cohort study involving 100 kidney transplant individuals. Individuals who are wait-listed to receive a kidney transplantation or have already received one will be included in this study. Individuals will undergo a battery of detailed neurocognitive tests at baseline (in part before surgery), and then 3 and 12 months afterwards. Furthermore, the enrolled patients will complete a validated German version of the Cognitive Failure Questionnaire for self-assessment (s-CFQ) as well as the Hospital Anxiety and Depression Scale -Deutsche (HADS-D), a self-report screening instrument with two scales that capture anxiety and depression. In addition, a hair sample will be taken at each measurement time point for the determination of hair cortisol levels as a parameter for the cumulative hypothalamic-pituitary-adrenocortical axis activity over the previous three months. The primary outcome measure will be (a) the effect of kidney transplantation on the cognitive performance up to 12 months after transplantation and (b) the course of cognitive performance following kidney transplantation over time.

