### Inclusion and exclusion criteria

Individuals who are scheduled to receive a kidney transplantation (immediate—deceased kidney donor, or within the following 2 weeks—living kidney donors) or have already received a kidney transplantation in the past will be included in this study. Due to the use of a standardized psychological assessment, individuals have to be native German speakers and at least 18 years of age. individuals under the legal supervision of a caregiver and with preexisting psychiatric disorders will be excluded from the study.

The study is divided into two parts (Table 1).

**Table 1 Tab1:** Trial schedule of enrollment and assessments

		Enrollment		Post-allocation	
Study Period, Part A					
Time point		*t*_−1_	*t*_1_	*t*_2_	*t*_3_
Enrollment					
Eligibility screen		X			
Informed consent		X			
Allocation		X			
Interventions					
Kidney transplantation			X		
Assessments					
ROCFT		X		X	X
VLMT		X		X	X
TMT-A		X		X	X
WMS-R-numbers forward		X		X	X
TMT-B		X		X	X
WMS-R-numbers backwards		X		X	X
RWT		X		X	X
Study period, Part B					
Time point	*t*_−2_		*t*_−1_	*t*_1_	*t*_2_
Enrollment					
Eligibility screen			X		
Informed consent			X		
Allocation			X		
Interventions					
Kidney transplantation	X				
Assessments					
ROCFT			X	X	X
VLMT			X	X	X
TMT-A			X	X	X
WMS-R-numbers forward			X	X	X
TMT-B			X	X	X
WMS-R-numbers backwards			X	X	X
RWT			X	X	X

Part A:

All included individuals undergo a detailed neurocognitive test battery on the day of transplantation (deceased kidney donation), or within 14 days before transplantation (living kidney donation). The neurocognitive test battery will be repeated after 3 and 12 months.

For individuals on the waiting list for deceased donor kidney transplantation we aspire to also carry out neurocognitive tests during standard visits to the hospital. Standard visits are typically several years apart and the date of transplantation is unforeseeable. Therefore, we expect not to be able to gather respective data for the majority of our participants and rather, will use it descriptively and for qualitative analyses.

Part B:

All included individuals who have already undergone transplantation and are in outpatient follow-up will undergo the same neurocognitive test battery as individuals in part A at baseline, after 3 months, and after 12 months.

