A likely mediator of the association between stress and cognitive performance, but also between depression and cognitive performance, is HPA axis activity, which is commonly assessed via its end-product cortisol. Excess cortisol has been found to have damaging effects on the limbic system, which leads to impairment of learning mechanisms [51]. Some studies also suggest that higher cortisol levels are associated with slower processing speed in persons suffering from depression [52, 53]. In line with this, one study found a negative association between hair cortisol and cognitive performance after stroke [54]. Hair cortisol as a marker of HPA axis activity is of special interest because it represents the cumulative HPA axis activity of the months before the time point of measurement [33] (in our case, before kidney transplant). However, we are not aware of any study that has investigated associations of subjective stress or hair cortisol, or their interaction with depression, in kidney transplant individuals.

Individuals who received kidneys from a deceased donor as well individuals who received living kidney donation will be investigated. In order to detect an effect of transplantation, testing will be performed close to the time of transplantation. Neurocognitive testing is performed in living kidney donor recipients within 14 days prior to planned transplantation. In individuals receiving postmortem donation, prior scheduling of neurocognitive testing is not possible. After individuals are placed on the waiting list, the waiting period for a deceased donor renal transplant usually ranges between 6 to 8 years in Germany [55] and around 4 years in the Eurotransplant region [56], making testing at listing impractical. Therefore, we decided to perform testing when we admit individuals for kidney transplantation during dialysis prior to transplantation. It has been shown that the test results are not affected by dialysis [57].

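### The prevalence sample is described as the consenting patients on a 142-person transplant list, but the eligibility criteria give listed patients with no imminent transplantation and no earlier graft no route into the study

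*Protocol article*

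**What the plan says.** The Sample size calculation opens with the prevalence aim, for which it will include "all individuals currently registered on the local transplant list", limited to those who can and do consent. It then gives the size of the list: "Currently, this list includes 142 individuals (75 individuals are in status T (transplantable), 67 individuals are in status NT (non-transplantable").

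The Abstract (Methods) describes a "prospective single-center cohort study involving 100 kidney transplant individuals" and says that people who are wait-listed or already transplanted will be included.

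The Inclusion and exclusion criteria are narrower. For people not yet transplanted they read: "Individuals who are scheduled to receive a kidney transplantation (immediate—deceased kidney donor, or within the following 2 weeks—living kidney donors"). The only other route is an earlier kidney transplant. Table 1 has two schedules, Part A and Part B, and each contains a transplantation. The text under Part A hopes to test patients on the deceased-donor waiting list at routine visits, expects no such data for most participants, and reserves the data for descriptive and qualitative use.

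The Statistical analysis section estimates prevalence as the proportion meeting the impairment criteria at each time point of a three-time-point design.

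**The concern.** A listed patient who has no transplantation in prospect within the stated window and has never had a graft is counted in the prevalence sample by one section and is not admitted by another. Non-transplantable patients are the clearest case, but the same holds for any transplantable patient to whom no organ is allocated during recruitment.

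What is at stake is the denominator and the target population of a stated aim. As written, the prevalence could refer to everyone on the list, to candidates selected by receiving an organ, to recipients, or to a mixture. Candidates who reach transplantation are a selected part of the list, so the proportion impaired at Part A baseline cannot be read as prevalence on the waiting list. A reader who takes the 142 at face value would make that reading.

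**Working it through.** **1. The plan's own figures.** The list adds up: 75 + 67 = 142. The section's other figure, N = 42, can also be reproduced. For a repeated-measures ANOVA with f = 0.20, m = 3 time points, k = 2 groups and α = 0.05, and assuming a correlation of ρ = 0.5 between measurements (the protocol gives none) and sphericity:

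- λ = N·m·f²/(1 − ρ) = 42 × 3 × 0.04 / 0.5 = 10.08
- df = m − 1 = 2 and (N − k)(m − 1) = 40 × 2 = 80
- power from the noncentral F distribution = 0.803

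Nothing in this calculation uses the 142, so N = 42 and the target of 50 stand apart from the present point.

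**2. Routes into the study for a person on the list.**

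| Listed patient | Sample size calculation | Inclusion criteria and Table 1 |
|---|---|---|
| Deceased-donor transplantation now, or living-donor transplantation within 2 weeks | counted | Part A |
| Listed again after an earlier graft | counted | Part B |
| Non-transplantable, no earlier graft | counted | none |
| Transplantable, no organ during recruitment, no earlier graft | counted | none |

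**3. Size of the last two rows.** The protocol does not give the number of listed patients who would qualify, so only bounds are possible.

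- Non-transplantable: at most 67 of 142 = 47%.
- Transplantable: recruitment runs from January 2021 to December 2022 (Trial status), about t = 2 years. The Discussion gives waits of 6 to 8 years in Germany and about 4 years in the Eurotransplant region. I apply these to the 75 and assume a constant transplant rate. The number reaching transplantation is then 75·t/w (steady state) or 75·(1 − e^(−t/w)) (exponential waiting time):

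| Wait w (years) | 75·t/w | 75·(1 − e^(−t/w)) |
|---|---|---|
| 8 | 18.75 | 16.6 |
| 6 | 25.0 | 21.3 |
| 4 | 37.5 | 29.5 |

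Roughly 17 to 38 of the 142 (12% to 27%) would enter Part A by this route. Living-donor recipients are not counted, because the protocol gives no number for them.

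**4. Consequence for a prevalence estimate.** The 95% half-width at an assumed prevalence of 50% is 1.96·√(0.25/n):

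| n | Half-width (points) |
|---|---|
| 142 (all listed patients take part) | 8.2 |
| 100 (cohort size in the Abstract) | 9.8 |
| 50 (follow-up target) | 13.9 |

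These are my figures. The protocol states no precision for prevalence.

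**The case against.** The best defence is that the document does not exclude listed patients consistently. The Abstract says wait-listed people will be included, and the text under Part A describes testing them at routine visits. That stands, and it rules out the flat statement that listed patients cannot enter the study. But it shows that the document disagrees with itself. It does not make the 142 recruitable under the criteria as written.

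Four stronger readings are tempting, and the document does not support them.

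- A reader might infer that 47% of the list is ineligible. That share is an upper bound on a snapshot: a non-transplantable patient may change status, and one with an earlier graft qualifies for Part B. Neither number is given. For the same reason one cannot say that no Part B patient is among the 142. The protocol also gives no split between Parts A and B, so the share of the cohort that Part B supplies is unknown.
- A reader might infer that the protocol overstates its precision. It states none, and it limits inclusion to those who can and do consent, so 142 is a ceiling and not a promised number.
- The Discussion's phrase "making testing at listing impractical" might be read as an admission that listed patients cannot be tested for prevalence. In context it explains why the pre-transplant baseline is taken close to surgery. It does not address a one-off prevalence test.
- The Abstract's 100 might be taken to contradict the 142. One is a cohort size and the other the length of a list. The 100 is not derived, but that is a separate matter.

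It is also fair to say that the primary outcome is cognitive performance over time in Parts A and B, and that prevalence is a descriptive proportion with no powered test. This limits the weight of the point without removing it.

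**Conclusion.** The inconsistency is real and limited in scope. The prevalence sample in the Sample size calculation cannot be recruited under the Inclusion and exclusion criteria and Table 1. Listed patients with neither an imminent transplantation nor an earlier graft have no route in. They comprise up to 67 non-transplantable patients and the transplantable patients who receive no organ in about two years. At the waiting times quoted in the Discussion, and assuming a constant transplant rate, that second group would be half or more of the 75 (37.5 of 75 at a 4-year wait in the steady-state calculation, more at longer waits), apart from any living-donor recipients and anyone with an earlier graft.

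The point concerns who is in the prevalence denominator and to whom the result applies. It does not touch the primary outcome, the N of 42 or the target of 50. It should be corrected before any prevalence is reported.

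**What to change.** Reconcile the Abstract (Methods), the Inclusion and exclusion criteria with Table 1, and the Sample size calculation, in one of two ways.

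1. Remove the 142-person list as the prevalence sample. State that prevalence is estimated in the enrolled cohort, separately for pre-transplant patients (Part A baseline) and post-transplant patients (Part A follow-up and Part B). Give the expected number in each, and make no claim to waiting-list prevalence. Bring the Abstract's wait-listed wording into line with the criteria. This costs rewording only and needs no extra patients. The downside is a smaller stated prevalence sample, with the half-widths shown above for 100 or 50 in place of 142, and wider still for the Part A baseline if fewer than 50 patients enter that part.
2. If waiting-list prevalence is the target, amend the criteria and Table 1 so that listed patients, whatever their status, can be admitted for one cross-sectional test. This keeps the list as the frame, at the cost of the added testing and a protocol amendment.

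Either way, the repeated-measures sample size stays as it is.

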### Primary outcome measure

The primary outcome measure will be cognitive performance. (a) We will compare cognitive performance before and after kidney transplantation, up to 12 months after transplantation in a population of patients who did not yet receive kidney grafts before enrollment in the study (part A) and (b) we will also investigate the development of cognitive performance over a period of 12 months in a population of patients who already received kidney grafts before enrollment in the study (part B).

### Secondary outcome measures

As a secondary outcome, we will assess a distinct profile of cognitive function using standard neurocognitive tests. Furthermore, we will explore the impact and temporal development of a set of risk factors for deficits in cognitive performance. Second, we want to examine the extent to which cognitive impairment affects depression at all follow-up time points. Third, we want to assess how stressors negatively or positively affect cognitive performance. Fourth, we want to investigate to what degree cognitive performance affects the formation and development of donor-specific antibodies.

## Discussion

The purpose of this study is to assess the extent and development of cognitive impairment in kidney transplant individuals and to provide a clear profile of cognitive function using standardized neurocognitive tests. Furthermore, we aim to evaluate whether transplantation per se leads to an improvement in cognitive performance.

There is currently no standardized test battery for kidney transplant populations, so we selected different validated tests to evaluate the different domains. Through this, it will be possible to create a neurocognitive profile of the investigated population. The tests used in kidney transplant individuals [10, 11, 41, 42] (Brief Cognitive State Examination, MoCA und 3MS, Modified Mini-Mental State Examination), which can be found in literature, are only screening tests and may underestimate the extent of cognitive impairment. We use a more comprehensive neurocognitive test battery, which is then also able to establish a neurocognitive profile in individuals after kidney transplantation. A recently published study showed a high prevalence of cognitive impairment in dialysis individuals [5], examined by the CERAD Test battery [43].

Anemia, secondary hyperparathyroidism, dialysis disequilibrium and uremic toxins (UT) have been reported as major causes of cognitive impairment accompanied by chronic kidney disease [44], as well as dialysis duration [45]. We assume that these parameters improve after transplantation and want to investigate the effect of these parameters on cognitive function.

Depression in hemodialysis individuals is characterized as one of the most common psychological aspects regarding studies on individuals with kidney failure [46]. To evaluate the frequency of depression and its effect on cognitive performance the HADS-D [26] Test will be performed. We also hypothesize that transplanted individuals suffering from depression display significantly higher cognitive impairment than transplanted individuals without depression. In one of our previous investigations, depression was significantly associated with a lower level of cognition [5]. Other studies have also found similar decline in cognition with the presence of depression [45, 47, 48]. This can be explained by the effects of symptoms of depression on domains of cognition like executive functioning and processing speed [48, 49]. A recent meta-analysis also shows that subjective stress influences the development of cognitive impairment [50].

A likely mediator of the association between stress and cognitive performance, but also between depression and cognitive performance, is HPA axis activity, which is commonly assessed via its end-product cortisol. Excess cortisol has been found to have damaging effects on the limbic system, which leads to impairment of learning mechanisms [51]. Some studies also suggest that higher cortisol levels are associated with slower processing speed in persons suffering from depression [52, 53]. In line with this, one study found a negative association between hair cortisol and cognitive performance after stroke [54]. Hair cortisol as a marker of HPA axis activity is of special interest because it represents the cumulative HPA axis activity of the months before the time point of measurement [33] (in our case, before kidney transplant). However, we are not aware of any study that has investigated associations of subjective stress or hair cortisol, or their interaction with depression, in kidney transplant individuals.

Individuals who received kidneys from a deceased donor as well individuals who received living kidney donation will be investigated. In order to detect an effect of transplantation, testing will be performed close to the time of transplantation. Neurocognitive testing is performed in living kidney donor recipients within 14 days prior to planned transplantation. In individuals receiving postmortem donation, prior scheduling of neurocognitive testing is not possible. After individuals are placed on the waiting list, the waiting period for a deceased donor renal transplant usually ranges between 6 to 8 years in Germany [55] and around 4 years in the Eurotransplant region [56], making testing at listing impractical. Therefore, we decided to perform testing when we admit individuals for kidney transplantation during dialysis prior to transplantation. It has been shown that the test results are not affected by dialysis [57].

Despite vigorous planning, the present investigation certainly contains some limitations. The test environment may not be optimal for the individuals who will receive the kidney from a deceased donor (patient might be more nervous than usual). It would have been more ideal to test those individuals 1 or 2 weeks before transplantation, but this is not possible, as it is not known when these individuals will receive their transplant offers. It seems possible that HADS responses may be influenced by the positive news of the transplantation. Here, however, it is likely that the influence might be more pronounced in individuals for whom transplantation is not planned (deceased donor kidney transplantation) than in those for whom transplantation is planned (living donation).

The results of our study could have potentially important implications for the prevention and treatment of cognitive impairment in kidney transplant individuals. By increasing our knowledge of the neurocognitive profile and assigning the corresponding deficits, it might be possible to create an individualized training program to positively impact cognitive deficits in these individuals.

### Trial status

The study is currently enrolling individuals. The local human research ethics committee of the Justus-Liebig-University of Giessen (AZ 195/20) approved this study. Recruitment started in Jan 2021 and is expected to be completed in December 2022. The study was registered with the German clinical Trials register under the number DRKS00029164.

## Data Availability

The datasets used or analyzed during the current study are available from the corresponding author on reasonable request.

## Abbreviations

sCFQ: Questionnaire for self-assessment
CKD: Chronic kidney disease
ESRD: End-stage renal disease
HADS-D: The German version of the Hospital Anxiety and Depression Scale
HPA: Hypothalamic-pituitary-adrenocortical
MCI: Mild cognitive impairment
MMSE: Mini-mental-state-Examination
NAsKiT: Neuropsychological Assessment of Cognitive Impairment in Kidney Transplantation
ROCFT: The Rey-Osterrieth Complex Figure Test
RWT: The “Regensburger Wortflüssigkeitstest
TMT: Trail Mark Test
VLMT: The “verbaler Lern- und Merkfähigkeitstest
